Mothers are female caregivers such as biological mothers, aunts, grandmothers, or guardians. We selected a pragmatic type II hybrid effectiveness design because it allows for a simultaneous assessment of the intervention implementation effectiveness and clinical outcomes assessment [39]. The study will be conducted among 612 mother-daughter dyads (*n* = 612 × 2 = 1,224 participants) recruited from 18 LGAs to a stepped-wedge randomized control trial of the crowdsourced intervention versus usual care. All mother-daughter dyads will be followed for 12 months. The Proctor’s Implementation Outcomes Framework [41] and the PEN- 3 cultural model [42] will guide the analysis and evaluation of the implementation process. We will recruit and train one CHW per LGA (*n* = 18) with one supervisor per LGA (n = 18) to assist with overall study implementation. Before participant recruitment, all CHWs will receive training on the final intervention, good clinical practice and human subject research. CHWs are key partners [43] that will recruit mother-daughter dyads meeting the eligibility criteria, identify barriers to engagement and participation, tailor and adapt the mother-daughter campaign to include access to onsite services for HPV self-collection kits, screen mothers and vaccination of girls by study nurses. CHWs will transport self-collected cervical samples to the NIMR laboratory, provide test results, link mothers to treatment for positive test results and retain participants overtime to advance efforts to eliminate cervical cancer in their LGAs. The trial is designed as a pragmatic study to closely mirror real-world conditions for on-going HPV prevention services in Nigeria.

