### Study setting aims and approach

#### Setting

Nigeria’s population is estimated at over 200 million, of which 49.3% are female [50, 51]. The country has 36 states mapped into six geopolitical zones with a Federal Capital territory [50]. There are also 374 distinct ethnic groups and indigenous languages spoken throughout its 36 states and Federal Capital Territory [50]. Data from the most recent Demographic Health Survey (2018) estimates that the median age at first sexual intercourse among women is 17 years of age and first marriage at 19 years [52]. Nearly half of women aged 25–49 give birth for the first time before age 21, while 19% of teenage women aged 15–19 have begun childbearing [52]. The Literacy rate in Nigeria is 60% [53]. Also, 65% of women aged 15–49 are employed or self-employed [52], while the monthly minimum wage is 30,000 naira ($18.4) [54]. Although HPV vaccine coverage has increased with the nationwide rollout at 75% [55], it remains notably below the 90% target needed to eliminate cervical cancer as a public health concern. Additionally, despite recommendations for routine cervical cancer screening for women aged 30–49, cervical cancer screening coverage remains under 10% [56, 57]. HPV self-sampling, a potentially accessible method for increasing screening uptake, is also not yet widely implemented or routinely practiced in Nigeria. Organized cervical cancer screening programs are limited, particularly in community settings where most individuals receive healthcare. Our partnership with the Nigerian Institute for Medical Research is critical for enhancing the feasibility of the study. As the key research hub within the Nigerian Ministry of Health, NIMR is well-positioned to design and deliver the intervention across the 18 recruited local government areas within the six geopolitical zones of Nigeria (See Fig. 1).

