#### Recruitment

We will enroll mother-daughter dyads in the 18 LGAS. Recruitment methods include in-person events and venue-based, participant referral, community, religious setting and school-based referrals, social media, and online referrals. First, mother-daughter dyads will be identified and recruited to participate in an upcoming Mother-Daughter Day event on HPV prevention methods. Second, those who agree to participate will receive reminder text messages before the event. Third, trained CHWs and supervisors will provide educational information and materials on cervical cancer control at the event.

Fourth, onsite services for HPV vaccination and self-collection kits will be offered to mother-daughter dyads, with girls receiving HPV vaccinations immediately in an onsite vaccination dedicated private space designated for the mother-daughter Day event. Mothers will receive instructions on self-collection in a private area, and their samples will be returned to the NIMR laboratory. Trained CHWs will provide the results of the samples, and those with positive results will be linked immediately to the supervisors for treatment and follow-up care, which we will track overtime. A baseline survey will be conducted among 612 mother/daughter dyads (*n* = 1,224 total) recruited in 18 LGAs (capped at 34 per area). We will define mothers as any female caregiver, including biological and surrogate mothers or close relatives who meet eligibility criteria. Eligibility criteria for mother-daughter dyads are outlined in Table 1. Trained community healthcare workers will approach and obtain consent from participants in a private space. Parental mobile phone numbers will be collected as tracking information for follow-up and retention.

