#### Randomization and rationale for stepped-wedge design

The 18 LGAs will be randomly allocated to the intervention, 4–5 LGAs per month for 12 months. All sites begin as part of the control condition and are block-randomized into four waves, with each wave beginning two months after the start of the prior wave and lasting for 6 months, followed by a 6-month follow-up period. All clusters will eventually receive the intervention, with outcomes measured every three months across all clusters. See Fig. 2for a schematic of the stepped-wedge cluster RCT design. Randomization will be conducted by the study statistician, who will not have direct contact with the LGAs. All LGAs will be informed of their assigned intervention wave before the first wave begins. Blinding was not implemented in this study, as all sites will eventually receive intervention, reflecting typical conditions in real-world settings. The stepped-wedge design was deemed acceptable and ethical by key program partners (NIMR and the Nigerian Ministry of Health) and study collaborators for logistical and pragmatic reasons, given the potential benefits of the intervention package (i.e., combined cervical cancer prevention strategies of vaccination and screening) and the equitable provision of the intervention to all sites [40].

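### Recruiting control-period dyads to a coming event with onsite vaccination may lead some to postpone it, lowering the control rate and biasing the daughters' effect upwards by an unknown amount

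*Protocol article*

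**What the plan says.** The comparison is the "crowdsourced intervention versus usual care" (Methods). Under Randomization and rationale for stepped-wedge design, "All sites begin as part of the control condition", the LGAs cross over in four waves two months apart, and outcomes are measured every three months in all clusters. The same section says "All LGAs will be informed of their assigned intervention wave before the first wave begins" and "Blinding was not implemented in this study".

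The Recruitment section gives one route into the trial. Dyads are "identified and recruited to participate in an upcoming Mother-Daughter Day event on HPV prevention methods", then "those who agree to participate will receive reminder text messages before the event", and at the event "onsite services for HPV vaccination and self-collection kits will be offered to mother-daughter dyads". No separate procedure is given for dyads enrolled while their LGA is in control, and the text does not say how long before the event they are enrolled.

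Data analysis describes a mixed model with repeated observations within subjects within LGAs and fixed effects for time and intervention status. Together with the three-monthly measurement, this implies that dyads are observed under control.

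Outside the trial the two services differ. The Setting section says "HPV vaccine coverage has increased with the nationwide rollout at 75" per cent. It also says that self-sampling is not in wide or routine use in Nigeria.

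**The concern.** A stepped wedge takes its control rate from clusters that are waiting. That rate represents usual care only if waiting does not itself change behaviour. Here the invitation that brings a dyad into the study also announces that vaccination is coming. A family that would otherwise have used the national programme has a reason to hold off.

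Postponement of this kind can happen only in LGAs that have not yet crossed over, so it coincides with control status. Randomizing the order of the waves does not help, because every LGA waits before its own step. The vaccination effect would then combine what the campaign adds with what the prospect of the campaign takes away from usual care. The cost-effectiveness results would inherit the same error. Once dyads have been invited in this way, no later analysis can separate the two parts.

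**Working it through.** **1. The plan's own figures.** Table 3 takes 10%, 15% and 20% as the control rate, with no allowance for deferral. I recomputed it with the Hussey–Hughes variance, using these inputs:
- 18 LGAs split 5/5/4/4 over four steps, giving five periods;
- 34/5 = 6.8 dyads per LGA and period, rounded up to 7;
- residual variance equal to the mean of p0(1−p0) and p1(1−p1);
- two-sided alpha 0.05 and power 0.80.

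| Control rate | Table 3 (ICC 0.005 / 0.01 / 0.05) | Recomputed |
|---|---|---|
| 0.10 | 0.216 / 0.220 / 0.235 | 0.218 / 0.221 / 0.235 |
| 0.15 | 0.283 / 0.285 / 0.300 | 0.283 / 0.286 / 0.301 |
| 0.20 | 0.342 / 0.346 / 0.362 | 0.343 / 0.347 / 0.363 |

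All nine agree within 0.002. The detectable differences run from 0.216 − 0.10 = 11.6 points to 0.362 − 0.20 = 16.2 points.

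**2. Why the time terms do not remove it.** Let c be the usual-care rate, d the share of it deferred while waiting, X the intervention indicator, β(t) the time effect and θ the true risk difference. If d is the same in all waiting clusters, the expected rate is

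c + β(t) + θX − cd(1−X) = (c − cd) + β(t) + (θ + cd)X.

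The coefficient of X becomes θ + cd. The inflation is cd, whatever β(t) is.

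**3. Size.** The documents give no d. I assume 0 to 0.50.

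| Control rate c | cd at d = 0 | d = 0.25 | d = 0.50 | Ceiling (d = 1) |
|---|---|---|---|---|
| 10% | 0 | 2.5 points | 5 points | 10 points |
| 15% | 0 | 3.75 points | 7.5 points | 15 points |
| 20% | 0 | 5 points | 10 points | 20 points |

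**4. Scale.** The expected vaccination rate is 65% (Sample size and power considerations), so the planned differences are 65 − 10 = 55, 65 − 15 = 50 and 65 − 20 = 45 points. Deferral of 50% would add 5/55 = 9%, 7.5/50 = 15% and 10/45 = 22% to them. Against Table 3's detectable difference at 15% and ICC 0.01 (28.5 − 15 = 13.5 points), 7.5 points is 56%.

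**5. Odds ratio.** The model uses a logit link. At 65% against a true control rate of 20%, the crude odds ratio is (0.65/0.35)/(0.20/0.80) = 7.4. With 25% deferral the observed control rate is 15% and the ratio is 10.5. With 50% it is 10% and the ratio is 16.7.

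**6. Mothers.** The mothers' outcome counts only specimens received at the NIMR laboratory (Outcomes). With self-sampling hardly available outside the trial, c is likely to be close to zero for them, and so is cd.

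**The case against.** The strongest reply is that the documents show the conditions for postponement, not postponement itself. Much of that stands.

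- **Who is told, and when.** LGAs, not families, learn the wave. The article does not say that control dyads are invited long before their event; if invitations go out shortly before it, there is little time to wait. But the only recruitment route described already tells families that an event is coming, and no safeguard is described.
- **Price.** A reader might infer that families wait for a free dose. The article uses that word for the national rollout, not for the trial event, so a price advantage is not documented.
- **Double counting.** It is tempting to say that deferred doses count twice, lowering the control rate and raising the intervention rate. The outcome is one dose within six months of enrolment, observed repeatedly in the same girl, and a girl vaccinated under control remains vaccinated after crossover. On that cumulative reading only the control-side shortfall applies.
- **A minimum bias.** No positive figure can be called a minimum, because zero deferral is equally compatible with the documents.
- **Who is left to defer.** Recently vaccinated girls are excluded (Table 1), so participants come largely from those the rollout missed, and few may have sought vaccination while waiting.
- **Opposite direction.** Enrolment contact and the baseline survey could prompt control-period uptake and bias towards no effect.
- **Onsite records.** The Abstract ascertains vaccination from onsite records. Read literally, a dose from the national programme would never count, so deferring it could not lower the control rate. That reading sits badly with the 10–20% baseline rates in Table 3 and with the Discussion, which refers to clinic records.

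The reply limits the claim to a possible bias, mainly for one outcome. It does not show that the design prevents it.

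**Conclusion.** The concern holds as an unaddressed risk of anticipation bias in the daughters' vaccination outcome. Its size is unknown. With 0–50% of control-period uptake deferred, the risk difference would be too large by 0–5, 0–7.5 or 0–10 points at control rates of 10%, 15% or 20%. These figures rest on the assumed deferral range, on Table 3's baseline rates being true usual-care rates among enrolled girls, and on dyads being enrolled and invited during control periods, which the article implies but does not state.

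A reader might infer that the trial could show a large effect from waiting alone. The figures do not support that: the inflation cannot exceed the control rate (10 to 20 points), against planned differences of 45 to 55 points. The threat is to the size of the estimate and what is built on it. Nor should the point be extended to the mothers' outcome, where there is little usual-care uptake to postpone. The net direction is not certain, since study contact may raise control uptake. The change is worth making because it is cheap and the bias cannot be undone in analysis.

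**What to change.** In the Recruitment section:
- separate enrolment and the baseline survey from the event invitation;
- send event invitations, dates and reminder texts only once the LGA's wave has opened;
- tell control dyads at enrolment that usual vaccination and screening services remain open to them now.

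In Randomization and rationale for stepped-wedge design, where planning allows, stage the disclosure so that LGAs do not all learn their wave before wave 1.

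The first three changes cost a revised recruitment script. Staged disclosure also shortens planning notice for waves 2–4. Each LGA has to train a community health worker and a supervisor and adapt the campaign, so the length of notice is a trade-off for the trial team.

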**Fig. 2 Fig2:**
[figure not shown]
Stepped wedge study design

#### Outcomes

Among daughters, the primary outcome will be HPV vaccination receipt (one dose) within 6 months of trial enrollment. Vaccines will be provided onsite at the Mother-Daughter Day campaign by study nurses following similar procedures for HPV vaccination during the national rollout [61]. Among mothers, the primary outcome will be self-collection completion within 6 months of trial enrollment, which will also be operationally defined by the receipt of specimens at the NIMR laboratory. As a secondary outcome, we explore HPV vaccine confidence, hesitancy and screening confidence, and the linkage to follow-up care and treatment of women with positive HPV results will be tracked. Using the validated Weiner's surveys, we will assess the acceptability and appropriateness of intervention components from both the daughters'and mothers'perspectives [62]. These surveys include 4 items, each scored on a 5-point scale [62]. Penetration will be explored using the Levels of Institutionalization Scale [63] to assess the extent to which components of the mother-daughter HPV campaigns are institutionalized within participating local government areas. We will also assess plans for sustaining [59] intervention components that will include 3-item leadership support for implementing the HPV campaign, a 3-item scale on responsiveness to mother-daughter preferences and needs for HPV preventive campaigns, an 8-item scale on coalitions, and partnerships to sustain the project, the 9-item infrastructure and capacity to support sustainability and the 3-item monitoring and evaluation tool from the sustainment measure on a 5-point scale [64]. We will also assess the intervention fidelity [65] and track adaptations made using the FRAME-IS [66] tool for reporting adaptation across the 18 LGAs.

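### The six-month-from-enrolment primary endpoints do not line up with waves that start two months apart, and enrolment is not tied to each LGA's crossover

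*Protocol article*

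**What the plan says.** The Outcomes section of the protocol article starts the clock for both primary outcomes at enrolment. For daughters: "Among daughters, the primary outcome will be HPV vaccination receipt (one dose) within 6 months of trial enrollment". For mothers, "the primary outcome will be self-collection completion within 6 months of trial enrollment". The abstract gives the same window.

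The section on randomization sets condition by calendar. "All sites begin as part of the control condition", and the LGAs are then "block-randomized into four waves, with each wave beginning two months after the start of the prior wave and lasting for 6 months", with six further months of follow-up. Outcomes are to be measured every three months in all clusters. The same section also states: "The 18 LGAs will be randomly allocated to the intervention, 4–5 LGAs per month for 12 months".

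The Data analysis section compares pre- and post-intervention periods in a mixed model whose time factor has three levels: baseline, 3 months and 6 months. Elsewhere in Methods, "All mother-daughter dyads will be followed for 12 months".

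The text does not place enrolment relative to an LGA's crossover. The Recruitment section has dyads recruited for a forthcoming campaign event, which points to enrolment at the LGA's own wave. Twelve months of follow-up also equals six campaign months plus six follow-up months. On the other hand, a control start for all sites and measurement across all clusters point to enrolment of everyone at trial start. Fig. 2, the design schematic, is not available here.

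**The concern.** A stepped wedge needs each outcome to belong to control or to intervention. A six-month window covers three two-month steps, so a dyad's single yes/no result can include time under both conditions, or can close before the campaign reaches its LGA.

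At stake is which uptake counts. Uptake during a late wave's campaign may never enter the primary endpoint. Uptake from the campaign in a middle wave may sit in a window that began under control. If enrolment follows the campaign instead, the endpoint has no concurrent control, and the effect cannot be separated from calendar trends. The article itself describes a national vaccination rollout under way, so such trends are plausible.

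**Working it through.** **1. The plan's own power figure.** Table 3 can be reproduced with the Hussey–Hughes variance, using 18 LGAs, four steps, five periods and waves of 4, 4, 5 and 5:

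Var = Iσ²(σ² + Tτ²) / [(IU − W)σ² + (U² + ITU − TW − IV)τ²]

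- I = 18 and T = 5.
- U = 4·4 + 4·3 + 5·2 + 5·1 = 43.
- W = 4² + 8² + 13² + 18² = 573.
- V = 4·16 + 4·9 + 5·4 + 5·1 = 125.
- IU − W = 774 − 573 = 201.
- U² + ITU − TW − IV = 1849 + 3870 − 2865 − 2250 = 604.

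Example: baseline 0.10, follow-up 0.235, ICC 0.05.
- Average binomial variance = (0.0900 + 0.1798)/2 = 0.1349.
- With 7 observations per LGA per period (34/5 = 6.8, rounded up), σ² = 0.01927 and τ² = 0.05 × 0.1349/0.95 = 0.00710.
- Var = 0.00233, SE = 0.0482, and z = 0.135/0.0482 = 2.80.
- Power = Φ(2.80 − 1.96) ≈ 0.80.

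All nine detectable rates come back within 0.002 on this basis. With 34 observations per LGA per period, power would be about 100%, so that reading is excluded. Table 3 therefore behaves as if each period yields its own complete outcomes. A six-month window cannot be completed inside a two-month step.

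**2. Overlap of the endpoint window with each wave, all dyads enrolled at month 0.** The lead-in L before wave 1 is not stated in the text, so it is an assumption. Wave k starts at s = L + 2(k − 1). Control months in the window = min(s, 6); intervention months = max(0, 6 − s).

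| Wave | L = 0 (control/intervention) | L = 2 | L = 3 |
|---|---|---|---|
| 1 | 0/6 | 2/4 | 3/3 |
| 2 | 2/4 | 4/2 | 5/1 |
| 3 | 4/2 | 6/0 | 6/0 |
| 4 | 6/0 | 6/0 | 6/0 |

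- In each column two waves (8–10 LGAs) mix conditions.
- LGAs with no intervention time in the window: 4–5 of 18 for L = 0 (4 × 34 = 136 to 5 × 34 = 170 of 612 dyads, 22–28%); 8–10 of 18 for L = 2 or 3 (8 × 34 = 272 to 10 × 34 = 340, 44–56%).
- For wave 4, s = L + 6, which is at least 6 for any L. With two-month spacing and common enrolment, no lead-in brings wave 4's campaign inside the window.

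**3. Enrolment at each LGA's own wave.** Here s equals the enrolment date for every dyad: 6 intervention months and 0 control months in all 18 LGAs.

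**4. Staggered enrolment regardless of wave** (uniform, waves of equal size, an assumption). Enrolment over the first six months leaves 50% (L = 0) or 67% (L = 2) of windows straddling a crossover, with 0% or 8% wholly in control.

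**5. The analysed time points.** The last is month 6. Campaigns end at months 6, 8, 10 and 12 if L = 0, and at 8, 10, 12 and 14 if L = 2. At month 6, wave 4 is only starting (L = 0), or wave 3 is only starting and wave 4 has not begun (L = 2).

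**6. The monthly roll-out sentence.** At 4–5 LGAs a month, 18 LGAs are used up in about four months (18/4.5 = 4), which agrees neither with two-month spacing nor with 12 months. Taken literally as monthly steps with L = 0, the split would be 0/6, 1/5, 2/4 and 3/3. The last wave would then contribute, but no LGA would have a full control window.

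**The case against.** The strongest reply is that a stepped wedge does not need a full six-month control window for every dyad. Late waves acting as controls for early ones is how the design works, and the plan has repeated measurements and a model with intervention status and time. With waves at 0/2/4/6, waves 1 and 2 are exposed at month 3 while waves 3 and 4 are not. With waves at 2/4/6/8, waves 1 and 2 are exposed at month 6 while wave 4 is still control. These are concurrent randomised contrasts inside the window. The analysis section already speaks of pre- and post-intervention periods, the abstract refers to pre-implementation data for each LGA, and Fig. 2 may fix the timing.

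Much of this stands. A reader might infer that the endpoint cannot supply any control-versus-intervention contrast, or that almost no dyad has a clean control window. The documents do not support either as a general statement. The 3- and 6-month measurements give a partial contrast, and under common enrolment with two-month steps 22–28% or 44–56% of dyads have a full control window in the scenarios worked. The 0% figure belongs to own-wave enrolment, where late-wave uptake is inside the window, so the two problems arise mainly under different readings. Each LGA also switches only once; it is a new wave that starts every two months.

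What the reply does not remove is the mismatch. The dyads with a full control window are the same ones whose campaign uptake is left out. The period comparison in the analysis section is not the endpoint in the Outcomes section. Pre-implementation data for the same LGA give a before-and-after comparison, not a concurrent one. Fig. 2 might show the lead-in, but under common enrolment no lead-in repairs the fit.

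**Conclusion.** The point holds as a misalignment between endpoint, roll-out and analysed time points, all three of which are fixed in this article. Under common enrolment and two-month steps, two waves mix conditions and the last 4–5 LGAs (wave 1 at month 0) or 8–10 LGAs (wave 1 at month 2) add no intervention uptake to the primary endpoints; a partial contrast of early with late waves remains. Under own-wave enrolment there is no concurrent control.

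This rests on two-month spacing, on waves of 4–5 LGAs, and on lead-ins that are assumed because the text gives none. Which enrolment reading applies cannot be settled from the text. Under none of those examined can the six-month result be assigned cleanly to one condition, with both conditions represented, across all 18 LGAs.

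**What to change.** 1. State when dyads are enrolled relative to their LGA's crossover, and how long the control period before wave 1 lasts.
2. Define both primary endpoints by design period. Take the date of first HPV dose and the date of specimen receipt, and assign each to the LGA's condition on that date, among dyads not yet vaccinated or screened.
3. Extend the analysed time points to the end of each LGA's six-month campaign. With common enrolment this is month 12 if wave 1 starts at enrolment, and month 14 for wave 4 if wave 1 starts two months later.
4. Reconcile this with the three-monthly measurement, the 12-month follow-up and the sentence on monthly allocation of LGAs.

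The cost is mainly wording, with no extra participants. There are three qualifications. The abstract names only onsite clinical records for vaccination, so doses received elsewhere during control time would have to be asked about and dated at the planned visits. A period-based outcome among those still unvaccinated or unscreened is not the same quantity as a single six-month proportion, so the power statement should be checked against it. Follow-up beyond 12 months is needed only if enrolment is common and wave 1 starts after enrolment.
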